### Intervention protocol

The 12 week pedometer-driven walking intervention will be based on self-regulation theory (SRT) [101] and include goal setting, feedback, educational material, and the use of a step calendar for self-monitoring. Participants will be required to walk for at least five days per week to meet evidence based international guidelines that recommend adults to accumulate at least 30 minutes of moderate intensity activity, on at least five days/week, to achieve optimal health benefits [102].

#### **
*Educational materials*
**

Participants in both the walking (intervention group) and control groups will also receive standardised educational material that consists of written and graphical information describing the importance of walking as a PA for health benefits and prevention of disease [29,30].

#### **
*Goal setting*
**

At the beginning of each week, participants will receive a weekly email reminder about his or her step-count goal for that week based on their baseline walking activity level; the goal will aim to gradually increase the level of activities by 5% from their previous goal setting target with an aim to reach at least 10,000 steps per day at the end of the 12 week period. These targets are based on international guidelines for walking interventions [52]. However for those who reached 10,000 steps per day at any time during the program will be also encouraged to maintain and increase their physically active lifestyle.

#### **
*Step count and feedback*
**

Participants in the intervention group will receive permanent step-count feedback by looking at the digital display on the pedometer monitor. Participants will also receive personalized weekly emails about daily average step-count and additional health information, to encourage their adherence with the program.

#### **
*Step calendar*
**

Participants in the walking group will be given a diary to record their walks and note each day as to whether they are adhering to the program, the time of day, duration of the walk, the week’s step-count goal, and the number of steps taken at the end of each day.

### Control group

Participants randomly allocated to the control group will be encouraged to read the educational activity material and be asked to record any exercise they perform over the 12 weeks. At the completion of the 12 weeks, and at the follow up at 24 weeks, these participants will again wear the pedometer for one week to establish a weekly step count for comparison to baseline scores.

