### Screening

Potential participants will initially be screened for eligibility for entry into the randomized control trial by wearing the pedometer (Yamax Digi-walker SW-200) for seven consecutive days. Participants will be instructed on how to wear and use the pedometer at the assigned location on a waist band above the lateral hip during all waking hours, except for periods immersed in water (bathing, swimming), during certain sporting activities (playing basketball or soccer, etc.), or in bed at night. They will be instructed to reset the pedometer to zero at the beginning of each day, and remove it at the end of each day, record on a step calendar the date and the time pedometer was attached and also removed, and the total number of steps displayed on the pedometer at the end of each day.

Participants who have accumulated an average of 7,500 or more steps per day will be excluded before baseline assessment. In addition, the ability of the participant to be physically able to participate in walking program will be screened using the physical activity readiness questionnaire (PAR-Q) [69]: if a participant answers yes to one or more questions on the PAR-Q, they will be advised to consult their healthcare provider and that physician consent will be required prior to program participation.

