### Randomization

After successfully completing the baseline assessment and signing the informed consent form, randomization to one of the two groups will be performed using sealed envelopes. Participants will be invited to choose an envelope from a basket containing envelopes that allocate 50% of the sample for the intervention and the other 50% for the control groups: each will contain the group name for allocation, and the timetable of the study. Researchers and participants will be not be blinded to group allocation. The assessor for final outcome measurements will be blinded to group allocation until the final assessment is achieved. The flow of participants through the recruitment process and randomisation is presented in Figure 1.

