### Outcome measurements and methods

The outcome measurements will be made at baseline, immediately after the 12 week pedometer-driven walking programme (and equivalent for control group), and at the 3 month follow-up time point. Data from all outcome measures will be securely stored and only analysed once the trial is complete. The primary outcome measurements are quality of life, PA level, and functional capacity. Secondary outcome measures will include blood pressure (BP), body mass index (BMI), body fat percentage (BF), and waist circumference (WC).

#### **
*Health-related quality of life*
**

This will be measured using The Short Form 36 version2 (SF-36v_2_) questionnaire. The SF-36v_2_ has been widely used to measure quality of life in general and specific populations [70,71]. It has eight domains of health-related quality of life: physical functioning, role limitations resulting from physical health problems, bodily pain, social functioning, general mental health, role limitations resulting from emotional problems, vitality, and general health problems. The SF-36 questionnaire has been validated and is a reliable measure of physical and mental health that can be completed in five to ten minutes [71,72].

#### **
*Ambulatory activity levels PA*
**

Objective change in PA level will be measured using a pedometer. The Yamax Digi-walker SW-200(Yamax, Tokyo, Japan) will be used in this study. This model demonstrates acceptable reliability for research purposes in the adult population [73,74]. It was found to be the most accurate pedometer in counting steps, recording between 1-3% error within both free living and controlled laboratory settings [75-77]; it has been found to most accurately record at walking speeds of 80–107 m^.^min^-1^[78,79]. Each participant will also complete the International Physical Activity Questionnaire short form (IPAQ-SF), which was developed as an instrument to measure health-related physical activity in work age populations, and is a valid and reliable measure for monitoring population levels of physical activity [80-82]. The questionnaire consists of 7 items which provide information within various intensity levels including aerobic activities vigorous-intensity, cycling activities moderate-intensity, walking activities, and sitting time in the last seven days [80,83].

#### **
*Functional exercise capacity*
**

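### The primary step count is labelled objective but is read and written down by unblinded participants, serves as feedback and goal in one arm only, and has a defined post-baseline wearing week only for controls

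*Protocol article*

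**What the plan says.** All places are in the protocol article.

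- *Outcome measurements and methods*: "The primary outcome measurements are quality of life, PA level, and functional capacity". For activity level it adds: "Objective change in PA level will be measured using a pedometer". Outcomes are due at baseline, directly after the 12-week programme (with an equivalent time for controls), and three months later.
- *Screening*: in the seven-day week before baseline, every participant resets the device daily and enters on a calendar the on and off times and "the total number of steps displayed on the pedometer at the end of each day".
- *Randomization*: participants and researchers are not blinded. "The assessor for final outcome measurements will be blinded to group allocation until the final assessment is achieved".
- *Intervention protocol*: walkers get "permanent step-count feedback by looking at the digital display on the pedometer monitor". The count is also the weekly target, raised by 5% at a time toward at least 10,000 steps/day. Walkers keep a diary that holds "the week’s step-count goal, and the number of steps taken at the end of each day".
- *Control group*: controls note any exercise during the 12 weeks. At 12 and at 24 weeks, "these participants will again wear the pedometer for one week to establish a weekly step count for comparison to baseline scores".
- *Sample size*: no calculation was made for this trial. The effect it observes is to be used to size a fully powered one.

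**The concern.** A device count is objective only if the number that reaches the dataset does not pass through someone who knows the allocation and has a stake in the value. Here the participant reads the number and writes it down. In one arm that participant has spent 12 weeks comparing the same number with a goal. In the other arm the participant comes back to a visible step counter, with no wear described since baseline.

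Two errors can follow. Walkers may round or record toward the goal. Controls may walk more during a week of renewed self-observation. Both arise after randomisation, so adjustment for baseline cannot remove them. An assessor's blinding does not protect a figure that the participant supplies. What is at stake is the between-arm difference in steps/day, the outcome closest to the hypothesis, and the size of the next trial that is to be built on it.

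**Working it through.** **1. Measuring conditions, side by side**

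| | Walking arm | Control arm |
|---|---|---|
| Baseline week | open display, self-recorded | the same |
| Weeks 1–12 | open display as feedback, weekly goal, step diary | exercise record; no pedometer wear described |
| Outcome week at 12 weeks | not stated | one week of wear |
| Outcome week at 24 weeks | not stated | one week of wear |

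Baseline conditions are equal, so the problem lies in the post-baseline comparison. Self-recording is explicit for the baseline week and for the walkers' diary. For the controls' later weeks it is inferred, because they are said to wear the device again and no other read-out is described. No covered display, device memory or staff read-out appears anywhere.

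**2. What a differential error would do (illustration)**

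The article gives no size for the error and no power figure to reproduce. Inputs:
- n = 30 per arm (*Study design*).
- SD of change = 2,661 steps/day, from the workplace study cited in the *Introduction* (3,451 ± 2,661). That this is an SD of change, and that it applies here, are assumptions.
- Two-sided 5% level, normal approximation (assumed).
- Net differential error b = 0 to 1,000 steps/day (assumed).

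SE of the difference = 2,661 × √(2/30) = 687. The 95% half-width is 1.96 × 687 = 1,347 steps/day.

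With no true effect, the chance that the interval excludes zero is Φ(b/687 − 1.96) + Φ(−b/687 − 1.96):

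| b (steps/day) | b/SD | chance |
|---|---|---|
| 0 | 0 | 5.0% |
| 250 | 0.09 | 6.5% |
| 500 | 0.19 | 11.3% |
| 1,000 | 0.38 | 30.7% |

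**3. What it would do to the next trial (illustration)**

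Assume a true effect of 1,500 steps/day and 90% power. Then n per arm = 2 × (1.960 + 1.282)² × 2,661² / δ², where δ is the estimate carried forward and (1.960 + 1.282)² = 10.51.

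- δ = 1,500 (no error): 67 per arm.
- δ = 2,000 (inflated by 500): 38 per arm; actual power at 1,500 is 69%.
- δ = 2,500 (inflated by 1,000): 24 per arm; actual power 50%.
- δ = 1,000 (reduced by 500, if control reactivity dominates): 21.02 × 7.08 = 148.8, so 149 per arm, more than twice what is needed.

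**The case against.** Several objections are sound and limit the point.

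- A reader might infer that the walkers' 12-week value is taken from the intervention diary, while goals and emails are still running. The article does not say so. The *Abstract* and *Outcome measurements and methods* both place the assessment directly after the programme. Nor is any prompting described at the three-month follow-up.
- Extra walking produced by goals and feedback is the treatment effect, not bias. Only misrecording, or reactivity that differs by arm, counts as error.
- A reader might infer that the two errors cannot cancel, or that they favour the walking arm. Neither is shown. Over-recording would raise walkers and renewed reactivity would raise controls. Controls also wore an open display at baseline, so part of their reactivity sits on both sides of their change score.
- The sizes used above are assumptions. The *Statistical analysis* section lists means, SDs and confidence intervals, not a test.
- The word objective may only be meant to contrast the device with the questionnaire (IPAQ-SF) described in the same paragraph.
- An article may leave the walkers' outcome week to the full protocol.

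The last objection does not dispose of the matter. What the article does state is enough: an open display, self-recording by unblinded participants, use of that count as goal in one arm only, and the label objective. A fuller account of the walkers' week would not by itself change how the number is captured.

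**Conclusion.** The point holds as a measurement weakness that should be corrected, not as a demonstrated bias. The primary step count, as described, is a self-recorded reading. The roles of the display and the count differ between arms after baseline, and a defined outcome week is stated for one arm only. Arm-dependent error is therefore possible; its size and direction cannot be determined from the article.

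If the net error were 500 to 1,000 steps/day and the SD 2,661, the chance of a spurious interval would be about 11% to 31% instead of 5%. A follow-on trial could be sized at 38 to 24 per arm instead of 67 (true effect 1,500 assumed); an error in the other direction would oversize it. Feasibility status does not remove the concern, because the effect estimate is explicitly meant to be carried forward. Two of the three primary outcomes, quality of life and six-minute walk distance, do not use the step count and are not touched by this point.

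**What to change.** State one assessment procedure for both arms:

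- The same separate 7-day week at baseline, at 12 weeks (starting after the last goal email) and at three months post-intervention.
- Display covered, no daily reset and no daily step recording in those weeks.
- A wear log of dates and on/off times without step counts, so that the number of days worn stays known and non-wear is not mistaken for inactivity.
- The accumulated total read by the blinded assessor already planned, at 12 weeks as well as at follow-up, and divided by logged wear days. The baseline reading precedes randomisation, so staff can take it; the screening threshold is an average and can still be applied.
- A check beforehand that the device holds a full week's count. The daily reset instruction under *Screening* suggests that the count accumulates, but the article does not confirm it.

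The cost is tape or a sealed cover, revised participant instructions and one read-out per participant per time point. The downside is that daily totals are lost and walkers have no display feedback in those weeks.

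If the display cannot be covered, state the same outcome week for both arms and report the step count as self-recorded, not as objective, with this limitation declared.

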## Discussion

Although pedometer-driven walking has been increasingly investigated as a management strategy for chronic disease and workplace populations, there has been no previous study of their use as an intervention for meat processing workers. This study will focus on a walking program as a management strategy for those populations. Results of this feasibility study will be used to inform the development of a future fully-powered controlled trial of the effectiveness of this intervention in this population.

## Abbreviations

RCT: Randomized controlled trial; MSD: Musculoskeletal disorders; PA: Physical activity; PW: Pedometer-driven walking; CG: Control group; SFF: Silver fern farms; BP: Blood pressure; BMI: Body mass index; BF: Body fat percentage; WC: Waist circumference; SF-36v2: The short form 36 version2 questionnaire; IPAQ-SF: International physical activity questionnaire short form; HRQL: Health related quality of life; SW200: The Yamax Digi-walker pedometer SW-200(Yamax, Tokyo, Japan; 6MWT: The Six Minute Walk Test; SRT: Self-regulation theory; NZ: New Zealand; ACC: Accident Compensation Corporation.
